**Fig. 4 Fig4:**
[figure not shown]
PET bottles and ball in the bowling target area

Similar to conventional bowling, children will be conceded two throws per block of attempts, considering that in the 10th block the children will have the right to three attempts. The bottles knocked down in the first attempt of each block will be put in place again only after the children have concluded the throws in the second or third attempt (only for the 10th block). Each bottle knocked down will be worth a point. Throws failing to knock down pins will count as zero in the score and as mistakes, while successful attempts will be regarded as hits.

If children manage to knock down all bottles at once, they will achieve the Striker score, doubling it in the following attempt, and if they knock down all the bottles in two attempts of a block or in the three attempts of the 10th block they will attain the Semi-Striker score, receiving half the score of the following throw as surplus.

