### Bowling

This activity will be performed with the Wiimote control held in the fist, which serves as if it were the bowling ball. The aim is to perform the throws and try to knock down the highest number of pins. Two blocks of nine attempts will be performed. At the end of the 10th block, children will start a new session of two attempts each until the end of the 7-min period. Each throw knocking pins down will count as a hit, or as a mistake in the opposite case. Children who knock down all 10 pins at once will be considered Strikers and will double the score for the next throw, while those knocking down the 10 pins in two throws (first to ninth blocks) or three (10th block) will be considered a Semi-Striker, receiving half of the score they achieve in the next throw as a surplus.

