### Bowling

The game of bowling will be performed with the use of 10 PET bottles containing 600 ml of water each (Fig. 4), placed at a distance of 4.83 m for children aged 7 and 8 years, and at a distance of 6.03 m for those aged 9 and 10 years. The aim of the activity is to throw a 0.5-kg medicine ball towards the bottles and knock down the highest number possible at once (Fig. 4).

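### No-Wii bowling: bottles are reset only after the second or third throw, with no exception for a strike, so a first-throw strike is followed by an empty throw that voids the bonus or at least records a mistake

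*Protocol article*

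**What the plan says.** The rules are in the Protocol article, Experimental protocol no-Wii training, Bowling, including the text below Fig. 4.

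- **Equipment:** "The game of bowling will be performed with the use of 10 PET bottles". The stated aim is to fell as many as possible with a single throw.
- **Throws:** "children will be conceded two throws per block of attempts, considering that in the 10th block the children will have the right to three attempts".
- **Reset:** "The bottles knocked down in the first attempt of each block" are the ones covered, and they "will be put in place again only after the children have concluded the throws in the second or third attempt".
- **Points:** "Each bottle knocked down will be worth a point".
- **Misses:** "Throws failing to knock down pins will count as zero in the score and as mistakes".
- **Strike bonus:** when all bottles fall together, "they will achieve the Striker score, doubling it in the following attempt". The Wii Bowling section says of such children that they "will be considered Strikers and will double the score for the next throw".
- **Semi-Striker bonus:** clearing the bottles over the throws of a block adds half of the following throw's score.

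Under Secondary outcomes measures, Motor learning, the scores of the six games are summed at the second session and at the last session. Scores per game and per domain are also examined. The Interventions section has hits, mistakes and score counted for every activity.

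**The concern.** The reset rule and the strike bonus do not fit together. The bonus attaches to the throw after the strike, but the reset rule leaves that throw with nothing to hit. Read together, they give the best possible first throw no bonus and an extra recorded mistake, while a child who needs two throws gets a bonus earned at a full set of bottles.

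At stake are the no-Wii bowling game score, the Aiming and Catching domain score and the summed motor-learning score, all secondary. The hit and mistake counts are affected too, but they are a separate record. The MABC-2 primary outcome and the sample size are not touched.

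**Working it through.** The article gives no bowling total to reproduce, so the check is to score the written rule throw by throw.

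**Inputs** (no-Wii Bowling, except as noted): 10 bottles; 1 point each; 2 throws per block, 3 in the 10th; no reset within a block; a throw that fells nothing = 0 points and 1 mistake; Semi-Striker = half of the following throw added; strike = next throw doubled (wording of the Wii Bowling section). X is the number felled by the first throw of the next block.

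**One block, blocks 1 to 9, bonus included:**

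- First-throw strike: 10 + 2 × 0 = 10 points, 1 hit, 1 mistake.
- Two-throw clearance, for example 6 + 4: 10 + X/2 points, 2 hits, 0 mistakes.
- Difference: X/2 in favour of two throws, from 0 (X = 0) to 5 (X = 10; 10 against 15 points).

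**Running total including the next throw X:**

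| X | Strike: 10 + X | Two-throw clearance: 10 + 1.5X |
|---|---|---|
| 0 | 10 | 10 |
| 2 | 12 | 13 |
| 5 | 15 | 17.5 |
| 8 | 18 | 22 |
| 9 | 19 | 23.5 |

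At X = 0 the points tie, but the strike still has one hit fewer and one mistake more.

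**Ten-block illustration under the same rule:**

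- Strike in every block: 10 × 10 = 100 points; 10 hits; 9 + 2 = 11 mistakes, because the 10th block has two empty throws.
- 5 + 5 in every block: 100 + 9 × 2.5 = 122.5 points; 20 hits; 1 mistake (the empty third throw of the 10th block).
- 9 + 1 in every block: 100 + 9 × 4.5 = 140.5 points; 20 hits; 1 mistake.

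These are extremes that show the ordering, not forecasts.

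**A miss followed by all 10 on the second throw:** the throw after it is at a full set. If this counts as a strike, the total including X = 5 is 10 + 2 × 5 = 20, against 15 for the first-throw strike.

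**Other reading of the bonus:** if the 10 itself is doubled, a first-throw strike gives 20 points and exceeds the two-throw maximum of 15. The empty throw is still a mistake.

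**If a strike ended the block and the doubling applied to X:** 10 + 2X against 10 + 1.5X. At X = 5 that is 20 against 17.5, so the strike ranks higher whenever X > 0.

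**The case against.** The strongest reply is that the passage likens the activity to ordinary bowling, where a strike ends the frame. It also words the throws as something the child is granted rather than must use. A bonus on the following attempt makes sense only if bottles are standing, so a reset was probably intended. This stands as evidence of intent. It does not override an explicit reset sentence that covers every block and names no exception. If some therapists follow the analogy and others the text, scoring will vary between children.

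The sentence on the bonus is also ambiguous: what is doubled may be the strike's own score. That stands too, and it is why the loss of points is conditional. The recorded mistake is not conditional on this.

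Therapists are trained in the scoring of each game and use a specific form. Those materials are not shown and may already settle the matter, in which case the article only needs to match them.

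A reader might infer more than the document supports in three ways:

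- **That the rule biases the comparison against the no-Wii arm.** The late reset is stated only for that arm, but the arms use different tasks and point rules, and the same rule applies at pre-test and post-test. No direction follows.
- **That mistakes lower the motor-learning score.** That outcome is built from game scores. Hits and mistakes are counted, but nothing adds them to or subtracts them from the score.
- **That the effect is large.** No strike frequency is given. The task is a 0.5-kg ball thrown 4.83 m or 6.03 m at water-filled bottles by children selected for poor motor performance, so strikes may be uncommon. Bowling is one of six summed games, and one Frisbee throw can be worth 100 points.

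**Conclusion.** The point holds as a minor scoring defect. As written, a first-throw strike is always followed by a throw at no bottles, and a mistake is recorded for it under either reading of the bonus. If the bonus doubles the next throw, the strike earns 10 points against 10 + X/2 for a two-throw clearance: a loss of 0 to 5 points per strike, with a tie at X = 0. This contradicts both the strike bonus and the activity's aim.

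The conclusion assumes that the reset sentence is applied literally and that the child takes the second throw. The loss of points further assumes the Wii section's wording of the bonus. The aggregate effect on the secondary motor-learning outcome cannot be sized without a strike frequency.

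**What to change.** In the no-Wii Bowling text, add that:

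- a first-throw strike ends the block or, in the 10th block, that the bottles are reset at once;
- the doubling applies to the next throw at a full set;
- no mistake is recorded for a throw made with no bottles standing, which also covers the empty third throw after a two-throw clearance in the 10th block.

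Align the therapist scoring form. The cost is a sentence or two and a form check, with no extra staff or data, and is best done before the first scored session.

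Separately, reconcile the block structure in the Wii Bowling section, where two blocks of nine attempts are described alongside a 10th block. That is a wording matter of its own and does not bear on this point.

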### Bow and arrow

This activity will be performed with a plastic bow-and-arrow commercial set (Fig. 5a), including a 62-cm bow and the arrows, each one of 41 cm. The arrows end with a suction cup which sticks to the target (Fig. 5b), to indicate the score that each child achieves in the game.

**Fig. 5 Fig5:**
[figure not shown]
**a** Bow and arrow, **b** Target for bow and arrow

A wooden target, covered with an adherent plastic surface so that the suction cups at the tip of the arrows stick to it, will be used. It measures 41 cm in circumference, and it will be fixed to the wall with a 120-cm adjustable rope in front of the children, at their visual height, at a distance of 2.30 m for 7- and 8-year-old children and 2.97 for children aged 9 and 10 years. Each arrow hitting the target and sticking to a scoring area will count as a hit, while those not fixing to it as a mistake. Scores will be based on the scale displayed on the target itself, ranging from 1 to 10 points.

### Balance disk

This activity will be performed with a vinyl balance disk measuring 40 cm in circumference (Fig. 6) placed on the ground; the children will perform 14 different static balance postures on top of it (Table 4). The postures were based on, and adapted from, the Berg Balance Scale [28]. Children aged 7 and 8 years must maintain the postures for 15 s, while 9- and 10-year-old children must keep them for 30 s. Each posture performed correctly and for the time due will count as a hit, while unbalances, falls, stepping on feet or putting hands on the ground will be regarded as mistakes. In the second case, children must go to the following posture. Each hit will be worth 10 points, and at the end of the 14 postures, they will repeat the same sequence until the time is over.

**Fig. 6 Fig6:**
[figure not shown]
Balance disk

**Table 4 Tab4:** Sequence of movement for balance disk

Sequence of movements – Balance disk	
1 – Standing, without support, with feet shoulder-width apart	
2 – Standing, without support, feet together	
3 – Standing, without support, with preferential foot on the disk and the other suspended in the air (90° knee flexion)	
4 – Standing, without support, with unpreferential foot on the disk and the other suspended in the air (90° knee flexion)	
5 – Standing, without support, with preferential foot forward	
6 – Standing, without support, with unpreferential foot forward	
7 – Standing, without support, with preferential leg raised forward	
8 – Standing, without support, with unpreferential leg raised forward	
9 – Standing, without support, with preferential leg in hip abduction	
10 –Standing, without support, with unpreferential leg in hip abduction	
11 – Standing, without support, with feet shoulder-width apart, trunk flexion and arms forward	
12 – Standing, without support, feet together, trunk flexion and arms forward	
13 – Standing, without support, with feet shoulder-width apart and eyes closed	
14 – Standing, without support, feet together and eyes closed	

### Balance beams

This activity will be performed with three 3 m-long wooden beams, measuring 3 cm in height, parallel to the ground (Fig. 7), each one with a different width, therefore offering children various degrees of difficult. The widest stick measures 6 cm, the intermediary 4.5 cm and the narrowest 3 cm. Three wooden traverses measuring 15 × 1.5 × 5 cm will be placed at the beginning of each beam, 50 cm apart from one another. Children will have to move on each one of the beams, from the widest to the narrowest, stepping with one foot at a time, so that the heel of the front foot is close to the toes of the back foot.

**Fig. 7 Fig7:**
[figure not shown]
Balance beams

Each beam stepped correctly will count as a hit, and any fall, using the beam or the ground as a support, slipping or losing contact of the feet with the beam, touching the ground or not performing the steps with feet close will count as an error. Scores for beams stepped correctly are as follows: 10 points (6-cm wide beam), 15 points (4.5-cm wide beam) and 20 points (3-cm wide beam). At every unsuccessful attempt, children will go back to the beginning of the beam where the mistake occurred and start the route again, moving to the next beam after doing the correct movement on the previous one.

### Outcomes measures

All tests will be applied by trained evaluators, blind regarding the allocation of the children in the intervention groups. Evaluators will be professionals in the areas of physiotherapy, physical education, and occupational therapy. Each child will be assessed by the same person before and after treatment.

### Primary outcome measure

#### The primary outcomes of this study is the motor performance

##### Motor performance – MABC-2

The motor performance of the children will be assessed through the MABC-2 total standard score (TSS). As mentioned before, MABC-2 is considered a gold standard tool to identify motor performance problems in children from 3 years old. MABC-2 is divided in three different age bands: the band 1 for children aged from 3 to 6 years old; band 2 for children aged from 7 to 10 years old; and band 3 for children aged from 11 to 16 years old. There are eight tasks in total, three for the Manual Dexterity domain, two for the Aiming and Catching domain; and three for the Balance domain. Children received a specific score in each domain and their motor performance classification is based on total score and percentiles values. Children < 5° percentile present motor difficult; children < 16° percentile are at risk for motor difficult and children > 16° percentile have no motor difficult detected. According to the MABC-2 tester manual, each child spends about 30–40 min completing all tasks.

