## Abstract

**Background:**

Despite the benefits highlighted by motor interventions based on virtual reality for children with Developmental Coordination Disorder (DCD), there are still doubts as to whether these are greater than those obtained with conventional interventions due to the absence of systematized protocols, and lack of evidence. Here, we present a protocol to systematically compare the effects of two motor-training programs (one Nintendo® Wii-based and the other no-Wii motor activities) on the motor learning in children with DCD.

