More specifically, the use of the Nintendo® Wii in the rehabilitation of children with motor alterations has been promoted for ease of measuring the force applied and capturing pressure change available in the Wii Balance Board (WBB), besides the fact that the Wii motion control allows great stimulation of the hand-dexterity motor component [15, 16]. Balance, Aiming and Catching are the domains of the Movement Assessment Battery for Children (MABC), that are regarded as the gold standard for the identification of DCD in children [17]. These aspects make the Nintendo® Wii very useful as a VR resource for motor interventions in children with DCD.

At present, however, little evidence exists in the literature on comparisons between the benefits of VR training, such as Nintendo® Wii, and conventional interventions such as without Wii [18–20].

The handful of existing studies that compare interventions with and without VR for children with DCD still show limitations about evidence created by the VR intervention [19, 21–24]. Moreover, it is not clear whether one type of intervention offers greater gains than the other due to the shortcomings from the scarce previous studies already published. Based on a recent systematic review by Hickman et al. [25] evidence for advantages gained by a VR intervention for children with DCD are not consistent in relation to conventional therapy. The authors argued that due the heterogeneity of assessment tools and outcomes fair comparisons were not possible. So, we believe that in this study we might see fair comparisons because the tasks will be closely matched by motor domain target into the training protocol.

These limitations of present approaches hinder a well-informed conclusion as to whether training with VR is more effective than conventional training in children with DCD. In this paper we present a protocol for a randomized clinical trial to systematically compare two motor-training programs (with and without Nintendo® Wii) on motor learning in children with DCD.

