## Methods/design

### Design and general characteristics

The protocol consists of a clinical, randomized controlled, blinded trial with two arms: training with the Wii, and conventional training without the Wii. Therapists will undergo instructional training to become familiar with all protocol activities, as well as with the scoring system of each game. The instructional training will occur a month before the beginning of the trial, which has a total duration of 8 h, for 2 h weekly. Despite the rigidly structured task settings required over the sessions, the therapists will be allowed to display their skills as therapist in order to promote a motivational environment for the children during the sessions as well as a great relationship between therapist and patient. There will be different therapists in each of the two intervention protocols, professionals from the areas of physiotherapy, physical education, and occupational therapy. The therapists in the two groups have comparable backgrounds and skill sets. All therapist teams have the same experience with pediatric rehabilitation, around 4 years of experience in this field. Children fulfilling the inclusion criteria in the study will be randomly allocated by draw into one of the two intervention groups. The flow chart of the subjects which will be allocated in the study is shown in Fig. 1 (Additional file 1).

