### Secondary outcomes measures

#### Motor learning

Motor learning in children will be assessed by means of the score obtained in the games. Individual scores in each of the six games from the second session (pre-test) will be summated as well as those from the six games of the last session (post-test) to obtain the general measurement of motor learning due to the treatment.

Individual scores in each game and for domain will also be counted (Manual Dexterity, Aiming and Catching, and Balance), before and after intervention. With the purpose of analyzing whether some activities are better learned in one type of intervention than in another. A specific form will be available for each therapist fills this information in each session.

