### Sample size

Sample size was calculated using the G*Power Software (3.1.9.2 version, Germany) based on a pilot study (*n* = 6). The calculation was performed considering the within-group comparisons for the Wii group, a power of 80%, and an alpha of 5%. The MABC total score assessed before and after 12 sessions was considered the main outcome and then considered for the analysis. The effect size was 0.80 (baseline: 58.0 ± 8.7; post 12-session intervention: 65.5 ± 9.9). Therefore, a sample of 15 participants was required for each group. In order to account for possible dropouts, we increased the sample to 16.

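### The stated aim is motor learning, but the primary and sized outcome is MABC-2 motor performance, so the aim rests on an unsized secondary outcome scored on different tasks in each arm

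*Protocol article*

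**What the plan says.** **Aim.** The Background section of the abstract says the programs will be compared "on the motor learning in children with DCD". The last paragraph of the main Background repeats this: the trial is "to systematically compare two motor-training programs (with and without Nintendo® Wii) on motor learning in children with DCD".

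**Primary outcome.** Under Primary outcome measure: "The primary outcomes of this study is the motor performance". The instrument follows: "The motor performance of the children will be assessed through the MABC-2 total standard score (TSS").

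**Motor learning.** This stands under Secondary outcomes measures: "Motor learning in children will be assessed by means of the score obtained in the games". The six game scores of the second session are added up and set against the six of the last session. The section also intends to see whether particular activities are learned better under one program than the other. On recording: "A specific form will be available for each therapist fills this information in each session".

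**Who records.** Design and general characteristics: "There will be different therapists in each of the two intervention protocols". The opening of Outcomes measures says that tests are applied by trained evaluators blind to allocation.

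**Sample size.** "The MABC total score assessed before and after 12 sessions was considered the main outcome". The contrast is the within-group change in the Wii arm.

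**Discussion.** It expects evidence on both motor performance and learning.

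**The concern.** The protocol treats performance and learning as two constructs with two instruments. The Methods/design part of the abstract assigns MABC-2 to performance and game scores to learning, and the outcomes section keeps that split. The mismatch is therefore not a loose use of synonyms: the aim names one construct and the primary outcome measures the other.

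What is at stake is what the trial can conclude about its own stated question. Read literally, the answer would come from summed game scores. That outcome was not used for sizing, is not collected by the blinded evaluators, and comes from different tasks in the two arms. A between-program statement built on it would be hard to interpret whichever way it fell.

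**Working it through.** **1. Aim, outcome and sizing side by side**

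| Element | Section | Construct |
|---|---|---|
| Aim | Abstract (Background); Background, last paragraph | Motor learning |
| Primary outcome | Primary outcome measure | Motor performance, MABC-2 total standard score |
| Sizing | Sample size | MABC total score, pre-post |
| Secondary outcome | Motor learning | Summed game scores |
| Expected evidence | Discussion | Performance and learning |

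**2. Reproducing the sample size**

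Inputs from Sample size: means 58.0 and 65.5, SDs 8.7 and 9.9, effect size 0.80, power 80%, alpha 5%. Sidedness is not stated.

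- Effect size: pooled SD = √[(8.7² + 9.9²)/2] = 9.32, and 7.5 / 9.32 = 0.805. This agrees with 0.80.
- Paired t-test (noncentral t), d = 0.80, two-sided 5%, 80% power: n = 14.30, rounded up to 15. At n = 15 the noncentrality is 0.80 × √15 = 3.10 on 14 df, and power is 82.1%.

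The stated 15 is reproduced. Treating 0.805 as a paired effect size implies a pre-post correlation of about 0.5 (which gives 0.801). Every input is an MABC figure. No mean, SD or target difference for game scores appears anywhere, so no sample size for motor learning can be derived.

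**3. What the 80% covers**

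It covers a one-arm, pre-post change. The between-arm MABC-2 contrast is not sized either. As illustration, for a two-sided 5% two-sample t-test with assumed standardised differences, and 16 read as per arm:

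| Assumed between-arm d | Needed per arm for 80% | Power at 16 per arm | Power at 15 per arm |
|---|---|---|---|
| 0.8 | 26 | 59% | 56% |
| 0.5 | 64 | 28% | 26% |
| 0.3 | 176 | 13% | 12% |

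For d = 0.8 and 16 per arm, the noncentrality is 0.8 × √(16/2) = 2.26 on 30 df. The smallest difference detectable with 80% power is d = 1.02 at 16 per arm.

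**4. Whether game totals share a unit between arms**

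- Marble balance (Wii) gives 1 point per ball. Its counterpart, Balance disk, gives 10 points per posture.
- Tightrope walk scores its three parts 15, 20 and 10. Balance beams scores its three beams 10, 15 and 20. A full run is worth 45 in both, but partial success is valued differently.
- Table tennis is a game against a machine opponent in one arm and returns off a raised half-table in the other.
- Frisbee (10, 50, 100) and archery/bow and arrow (1 to 10) use the same nominal scale, but on a virtual task in one arm and a physical one in the other.
- Balance disk holds last 15 s at ages 7 and 8 and 30 s at ages 9 and 10. In 7 min = 420 s, ignoring transitions, the ceiling is 420/15 = 28 hits (280 points) against 420/30 = 14 hits (140 points). Even within the no-Wii arm, only a child's own change is readable.

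A difference in raw totals between arms thus mixes learning with the scoring rules.

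**The case against.** The strongest reply is that the outcome hierarchy is clear. Primary outcome measure, Motor learning and Sample size all agree that MABC is the main outcome and game scores are secondary. Sizing a trial on its primary outcome is normal, and an unsized secondary outcome is no defect in itself. The abstract's Methods/design and the Discussion both bring performance into the purpose, so the aim is worded inconsistently rather than as learning alone throughout. All of this stands, and it limits the point to the aim and to what may be concluded from game scores.

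Two stronger readings are therefore not supported. A reader might infer that either outcome could be put forward as the trial's answer; but one primary outcome is fixed in advance, which is the usual safeguard. A reader might also compute an error rate of 1 − 0.95² = 9.75% for two headline tests. That needs two co-equal, independent tests. The plan does not set up two co-equal tests, and independence is doubtful because the activities were chosen to resemble MABC-2 movements.

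On blinding, the evaluator statement can fairly be read as covering MABC-2 rather than the session forms, and the Wii itself computes the marble-balance score. This softens the apparent contradiction. It does not change the fact that therapists delivering one arm's program fill in the learning data.

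**Conclusion.** The point holds as a mismatch between the stated aim and the primary, sized outcome. As worded, the aim rests on a secondary outcome that has no sample-size basis, is recorded by therapists who know the arm, and has no common unit between arms, although the protocol intends to compare learning between programs. That the therapists know the allocation is inferred from their being assigned to one arm's protocol.

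The arithmetic behind 15 per group is sound for what it sizes. No size can be put on the motor-learning question. Moving the comparison to MABC-2 does not bring the stated 80% power with it: about 59% at 16 per arm is an illustration under an assumed between-arm d of 0.8, and smaller differences give less. The registry record is not available, so nothing is concluded about it. The point should be acted on: the change is cheap and determines which claims the trial can support.

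**What to change.** - **Aim.** In the abstract and the last paragraph of the Background, state that the primary objective is to compare change in MABC-2 total standard score between the two arms, with motor learning as a secondary objective.
- **Motor learning.** Report game-score change within each arm, and amend the sentence in that section that looks for activities learned better under one program so that it matches.
- **Claims.** State that any conclusion favouring one program rests on the between-arm MABC-2 result, not on raw game totals.
- **Sample size.** Say that the 80% power applies to the pre-post change in the Wii arm and not to the between-arm contrast, and give the power or detectable difference for that contrast under stated assumptions.
- **Score name.** Reconcile the total standard score in Primary outcome measure with the total score in Sample size.

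This needs no new data and no change of outcome. The cost is that the sponsor gives up a comparative headline on motor learning and states openly that the between-arm comparison is not covered by the stated power.
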